#### **Baseline data (1 month after swab result or hospital discharge)**

- Name of person filling in the questionnaire and relationship with the case.
- Sex/gender

- Ethnicity
- Medically diagnosed conditions prior to respiratory infection
- Symptoms of acute COVID-19 infection (first 14 days)
- History of confirmed SARS-CoV-2 tests

Collected by study staff:

- Vaccination history (confirmed on the Australian Immunisation Register)
- If hospitalised (from EMR):
  - Length of stay
  - Number of viral infections
  - Treatment, e.g., antivirals, antibodies
  - Pneumonia Y/N
  - ICU/HDU admission Y/N
  - Respiratory support Y/N

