Follow-up studies on MIS-C indicate that the majority of patients recover fully, including improvement of cardiac dysfunction. Some have suggested that PCC in children is a subclinical presentation of MIS-C. However, elevated markers of inflammation, a central feature of MIS-C, are uncommon in long COVID. Furthermore, there is limited evidence that immunomodulatory treatment, which is very effective in managing MIS-C, has a role in treating long COVID. There are some studies on low-dose naltrexone (LDN) that suggest some patients experience fewer number of symptoms, and improved clinical symptoms, however randomised placebo controlled trials are required. LDN can act as an immunomodulator in multiple autoimmune diseases and malignant tumors. Given the distinct differences between children and adults with COVID-19 infection, paediatric-specific research on PCC is essential.

In September 2022, a panel of 27 experts convened to establish a clinical case definition for the post-COVID-19 condition in children and adolescents, informed by the scientific data available at that time. This definition is expected to undergo revisions as further high-quality evidence emerges and our collective understanding of the condition deepens. The World Health Organization (WHO) defines PCC, as:

- Occurring in individuals with a history of confirmed or probable SARS-CoV-2 infection
- Symptoms last at least 2 months, initially occurring within 3 months of acute COVID-19
- Symptoms generally impact everyday functioning, such as changes in eating habits, physical activity, behaviour, academic performance, social functions (interactions with friends, peers, and family) and developmental milestones.
- Symptoms may be new onset following initial recovery from an acute COVID-19 episode or persist from the initial illness.
- They may also fluctuate or relapse over time.
- Workup may reveal additional diagnoses, but this does not exclude the diagnosis of post-COVID-19 condition.
- More frequently reported symptoms in children compared with controls are fatigue, altered smell/anosmia and anxiety. Other symptoms have also been reported.
- This definition can be applied to children of all ages, with age-specific symptoms and impact on everyday function considered.

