Existing literature recommends that longitudinal cohort studies include control groups and ensure the recording of symptoms at consistent follow-up intervals. It is also essential to consider pre-existing medical conditions. Our study design addresses the current shortfall in rigorously structured research.

Our research aims to inform clinical management for children and adolescents, as well as COVID-19 vaccine recommendations, and guide the introduction of interventional studies in South Australian children.

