#### Data from consented participants

Following consent, survey data will be collected from those enrolled using an online RedCap baseline questionnaire to be completed at recruitment, followed by questionnaires at 3, 6, and 12 months post-infection. The WCHN study team will validate the positive test results of consented participants with CDCB. Questionnaires will be available for parents/carers or participants to answer where applicable. Quality of life questions will be available in two of the fastest-growing non-English languages used at home in South Australia: Mandarin, and Vietnamese. The survey is based on the International Severe Acute Respiratory and Emerging Infection Consortium (ISARIC) COVID-19 Paediatric follow-up protocol and questionnaire. If there is no response from a survey after one week, 2 reminders will be sent a week apart. Data will be collected using a secure password-protected web application housed on a SA Health data server (RedCap).

Data to be collected includes:

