### **3, 6, and 12 months (Online surveys)**

- Name of person filling in the questionnaire and relationship with the case.
- PCR/RAT tests and results since the last survey
- New conditions diagnosed by GP since the last survey
- Physical or mental health symptoms since the last survey
  - List of common long COVID symptoms, including questions about symptom intensity, based on the ISARIC Global Tier 1 Ongoing COVID-19 Follow-Up Survey symptom list.
  - Malmo POTS Score (MAPS).
  - Medical follow up of these symptoms
- Days absent from school, work, or higher education in the last month
- Conditions that have required follow-up with a GP
- Readmission to hospital
- Pediatric quality of life inventory (PedsQL) short form. The 15 items in the PedsQL comprise four Generic Core Scales (for ages 2 to 18):
  - Physical Functioning
  - Emotional Functioning
  - Social Functioning
  - School Functioning
- The PedsQL Multidimensional Fatigue Scale is composed of 18 items across three dimensions.

- General fatigue
- Sleep/rest fatigue
- Cognitive fatigue

Collected by study staff:

- If hospitalised with respiratory illness (From EMR):
  - Length of stay
  - Number of viral infections
  - Treatment, e.g., antivirals, antibodies
  - Pneumonia Y/N
  - ICU/HDU admission Y/N
  - Respiratory support Y/N

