| Demographic details                           |                                             | x                      |                        |                        |                         |
| History of COVID-19 infection                 |                                             | x                      | x                      | x                      | x                       |
| Medical history                               |                                             | x                      | x                      | x                      | x                       |
| Symptoms of acute infection                   |                                             | x                      |                        |                        |                         |
| Physical and mental health symptoms           |                                             | x                      | x                      | x                      | x                       |
| Medical follow up of symptoms                 |                                             |                        | x                      | x                      | x                       |
| Vaccination history (from AIR)                |                                             | x                      |                        |                        |                         |
| Days absent from school/work                  |                                             | x                      | x                      | x                      | x                       |
| GP presentations since the last survey        |                                             |                        | x                      | x                      | x                       |
| Information from EMR if hospitalised          |                                             |                        |                        |                        |                         |
| • Length of stay                              |                                             |                        |                        |                        |                         |
| • Number of viral infections                  |                                             |                        |                        |                        |                         |

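### No listed survey item records whether a symptom predates the infection, so the quoted onset criterion for PCC cannot be applied from the listed data

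*Protocol*

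**What the plan says.** **Definition.** Protocol section 3.c quotes the WHO case definition. Symptoms must last at least two months and must start within three months of the acute illness. It adds: "Symptoms may be new onset following initial recovery from an acute COVID-19 episode or persist from the initial illness". Section 4.c refers to a case definition for PCC and takes the primary outcome from survey responses and follow-up. For influenza, section 3.c says that no equivalent definition exists.

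**Surveys.** Section 5.c introduces its item lists with "Data to be collected includes" and says that the survey is based on an ISARIC paediatric questionnaire, which is not reproduced.
- Baseline is taken about one month after the swab or discharge. The list names "Medically diagnosed conditions prior to respiratory infection", symptoms of the first 14 days of acute illness, and earlier SARS-CoV-2 tests.
- At 3, 6 and 12 months the list names "Physical or mental health symptoms since the last survey", with intensity.
- Table 1 has a row "Physical and mental health symptoms" marked at baseline as well as at 3, 6 and 12 months. The section 5.c baseline list has no matching item, and no recall window is given.

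**The concern.** Diagnosed conditions are an incomplete proxy for symptoms that were already present. A child with undiagnosed chronic headache, poor sleep, fatigue or anxiety has no diagnosis to report, yet can report the symptom at every survey. A child with a diagnosed condition may have a symptom that is truly new. In neither case do the listed items date the onset.

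The primary estimate is an absolute incidence, so any old symptom counted as a case adds to it directly. The same background would enter the influenza cohort and dilute the objective 2 relative risk. Misplaced children would also blur the PCC and PAS comparisons in objectives 4 to 6 and could distort the objective 3 prediction model. The protocol's own literature review says of cohort studies in this field: "It is also essential to consider pre-existing medical conditions". An analysis plan can set the counting rule, but it cannot recover a variable that was not collected.

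**Working it through.** **1. What each listed item can show about onset**

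| Item | Period covered | Identifies a symptom present before infection? |
|---|---|---|
| Diagnosed conditions (baseline list) | Before infection | Only through a diagnosis |
| Acute symptoms (baseline list) | First 14 days of illness | No |
| Symptom row at baseline (Table 1) | Not stated | Not stated |
| Symptoms at 3, 6 and 12 months | Since the previous survey | No |

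No listed item supplies what the onset criterion needs.

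**2. The plan's precision figure**

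Section 8.b gives 0.62% to 1.47% for incidences of 1% to 6%, with 1,222 cases and 20% loss. Half-width = 1.96 × √(p(1 − p)/n).
- n = 1,222 × 0.8 = 978: 0.62 points at p = 1%, 1.07 at 3%, 1.49 at 6%.
- n = 1,000 (the Table 2 row): 0.62 points at 1%, 1.47 at 6%.

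The figures reproduce as half-widths, although the text of section 8.b calls them the width of the interval. The finite correction for 360,000 children changes nothing of note.

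**3. Bias in the incidence**

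Let t be the true PCC incidence and b the share of the other children whose old symptom is counted as PCC. Observed = t + (1 − t) × b. The protocol gives no value for b, so the range below is an assumption.

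| b | t = 1% | t = 3% | t = 6% |
|---|---|---|---|
| 0.5% | 1.5% | 3.5% | 6.5% |
| 1% | 2.0% | 4.0% | 6.9% |
| 2% | 3.0% | 4.9% | 7.9% |
| 5% | 6.0% | 7.9% | 10.7% |
| 10% | 10.9% | 12.7% | 15.4% |

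Example: t = 1%, b = 1% gives 0.01 + 0.99 × 0.01 = 0.0199.

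Bias divided by the half-width at n = 978, for t = 1%, 3% and 6%:
- b = 0.5%: 0.8, 0.45, 0.3
- b = 1%: 1.6, 0.9, 0.6
- b = 2%: 3.2, 1.8, 1.3

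**4. Relative risk in objective 2**

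With equal b in both cohorts, observed RR = [t₁ + (1 − t₁)b] / [t₂ + (1 − t₂)b]. For an illustrative true RR of 2.0:
- 6% v 3%: b = 1% gives 0.0694/0.0397 = 1.75; b = 2% gives 0.0788/0.0494 = 1.60; b = 5% gives 0.1070/0.0785 = 1.36.
- 3% v 1.5%: b = 2% gives 0.0494/0.0347 = 1.42; b = 5% gives 0.0785/0.0643 = 1.22.

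**The case against.** A reader might infer that no survey asks about pre-infection symptoms at all. The protocol does not support that. Its lists are not exhaustive, they give topics and not item wording, and the questionnaire is not shown. A question on prior status may already be there, or may lie behind the Table 1 baseline row. That limits the point to the listed items.

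A reader might also infer that long-standing symptoms *are* counted as PCC. The quoted definition would exclude them if onset were known, it generally expects an effect on daily functioning, and ascertainment includes follow-up. So the claim is only that they *may* be counted. These safeguards are partial. Functional impact does not date a symptom. The telehealth contact in Appendix B reaches severe symptoms not yet medically assessed, or low PedsQL scores, and serves referral.

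The larger biases in the table are not findings about this study. They assume that 5% or 10% of other children are misclassified, with no onset or impact filter, and nothing in the protocol supports those rates.

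Two further objections stand. A cohort enrolled on a positive test cannot have a prospective pre-infection baseline, so the timing of Survey 1 is not itself a fault. And with equal background in both cohorts a risk difference would largely cancel it, since the difference becomes (t₁ − t₂)(1 − b). But the plan specifies a relative risk, and the primary outcome is an absolute incidence without an uninfected group.

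**Conclusion.** The concern holds in limited form. The listed data do not allow the quoted onset criterion to be applied, and long-standing undiagnosed symptoms may enter PCC and PAS. The bias would run upward for the 3-month incidence and, with equal misclassification in both cohorts, towards 1 for the relative risk.

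The size is hypothetical because b is assumed. A small value is enough to matter at the low end of the planned range: b = 1% doubles a true 1%, a bias above the 0.62-point half-width. At b = 2% the bias exceeds the half-width over the whole 1% to 6% range. At b = 0.5% it stays below the half-width throughout. The point falls away if the questionnaire already records prior status and the definitions use it.

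**What to change.** - **Collect.** At Survey 1, add one response for each listed symptom on its status before this infection: absent, present and unchanged, or present but now worse. At later surveys, ask it only for symptoms first reported then. If the questionnaire already asks this, say so in section 5.c.
- **Define.** Count only new or worsened symptoms towards PCC and PAS, by the same rule in both virus groups. Report the unrestricted count as a sensitivity analysis.
- **Reconcile.** Make the section 5.c baseline list agree with the Table 1 symptom row, and state that row's recall window.

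**Cost.** One extra tick per symptom in an online form, so slightly longer surveys, and a sentence in the outcome definition. The answers are retrospective. Recall at Survey 1 spans one to about three months, because eligibility runs to two months after the test in the synopsis and three months in section 6.a. It is longer for symptoms first reported later. Current symptoms may colour the answer, which is why it is best taken once, early.

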### **3, 6, and 12 months (Online surveys)**

- Name of person filling in the questionnaire and relationship with the case.
- PCR/RAT tests and results since the last survey
- New conditions diagnosed by GP since the last survey
- Physical or mental health symptoms since the last survey
  - List of common long COVID symptoms, including questions about symptom intensity, based on the ISARIC Global Tier 1 Ongoing COVID-19 Follow-Up Survey symptom list.
  - Malmo POTS Score (MAPS).
  - Medical follow up of these symptoms
- Days absent from school, work, or higher education in the last month
- Conditions that have required follow-up with a GP
- Readmission to hospital
- Pediatric quality of life inventory (PedsQL) short form. The 15 items in the PedsQL comprise four Generic Core Scales (for ages 2 to 18):
  - Physical Functioning
  - Emotional Functioning
  - Social Functioning
  - School Functioning
- The PedsQL Multidimensional Fatigue Scale is composed of 18 items across three dimensions.

- General fatigue
- Sleep/rest fatigue
- Cognitive fatigue

Collected by study staff:

- If hospitalised with respiratory illness (From EMR):
  - Length of stay
  - Number of viral infections
  - Treatment, e.g., antivirals, antibodies
  - Pneumonia Y/N
  - ICU/HDU admission Y/N
  - Respiratory support Y/N

**Table 1. Study time points**

| Information collected                         | Waiver of consent
(Phase 1
WCHN only) | Survey 1
(Baseline) | Survey 2
(3 months) | Survey 3
(6 months) | Survey 4
(12 months) |
|-----------------------------------------------|---------------------------------------------|------------------------|------------------------|------------------------|-------------------------|
| Name                                          | x                                           |                        |                        |                        |                         |
| Date of birth                                 | x                                           |                        |                        |                        |                         |
| Postcode                                      | x                                           |                        |                        |                        |                         |
| Mobile phone number                           | x                                           |                        |                        |                        |                         |
| Swab date and details                         | x                                           |                        |                        |                        |                         |
| Hospitalisation information                   | x                                           |                        |                        |                        |                         |
| • Admission to hospital                       |                                             |                        |                        |                        |                         |
| • Discharge status                            |                                             |                        |                        |                        |                         |
| • Related to viral infection (Y/N)            |                                             |                        |                        |                        |                         |
| Consent and assent (if applicable)            |                                             | x                      |                        |                        |                         |
| Demographic details                           |                                             | x                      |                        |                        |                         |
| History of COVID-19 infection                 |                                             | x                      | x                      | x                      | x                       |
| Medical history                               |                                             | x                      | x                      | x                      | x                       |
| Symptoms of acute infection                   |                                             | x                      |                        |                        |                         |
| Physical and mental health symptoms           |                                             | x                      | x                      | x                      | x                       |
| Medical follow up of symptoms                 |                                             |                        | x                      | x                      | x                       |
| Vaccination history (from AIR)                |                                             | x                      |                        |                        |                         |
| Days absent from school/work                  |                                             | x                      | x                      | x                      | x                       |
| GP presentations since the last survey        |                                             |                        | x                      | x                      | x                       |
| Information from EMR if hospitalised          |                                             |                        |                        |                        |                         |
| • Length of stay                              |                                             |                        |                        |                        |                         |
| • Number of viral infections                  |                                             |                        |                        |                        |                         |
| • Treatment e.g., antivirals, antibodies      |                                             | x                      | x                      | x                      | x                       |
| • Pneumonia Y/N                               |                                             |                        |                        |                        |                         |
| • ICU/HDU admission Y/N                       |                                             |                        |                        |                        |                         |
| • Respiratory support Y/N                     |                                             |                        |                        |                        |                         |
| Pediatric quality of life inventory (PedsQL). |                                             |                        | x                      | x                      | x                       |
| PedsQL Multidimensional Fatigue Scale         |                                             |                        | x                      | x                      | x                       |

#### d. CONSUMER ENGAGEMENT

The study has two consumers with lived experience of caring for a child with ongoing sequelae following COVID-19 infection. The consumers have undergone an onboarding session to become WCHN Consumer Advocates. They have agreed to the role requirements and have signed necessary agreements, including codes of conduct and confidentiality.

The consumers will meet regularly with the Principal Investigator, who will report their feedback to the investigator team. They will also meet with the investigator team at regular intervals. The consumer advocates will be involved in reviewing all study material, including the protocol, PI sheet, consent form, questionnaires, and communications with potential participants and participants. The consumers will also be involved in interpreting results, planning communication strategies, and disseminating the results. The consumers are reimbursed for their time according to the standard consumer sitting fee of the WCHN consumer advocates.

